### Embedded qualitative study

#### Design

A qualitative descriptive approach based on the work of Sandelowski [64] will be used to capture key stakeholders views as to the acceptability and feasibility of respective study procedures, including the recruitment process, intervention content and delivery, data collection methods, as well as on the factors that facilitated or hindered engagement and adherence. This data will help identify any feasibility issues, which may need to be addressed to inform the design of a subsequent RCT.

A sample of participants with dementia (*n* = 5) and caregivers (*n* = 5) will be interviewed during the delivery of the CST programme and caregiver programme respectively (weeks 4–5). In addition, a sample of participants with dementia (*n* = 5) will be interviewed during the delivery of the physical exercise programme (weeks 11-12). These interviews will focus on capturing the ongoing perceptions and experiences of participants as they progress through the intervention. All participants will be interviewed post-intervention. Interviewing some participants during and post- intervention will provide information as to how the intervention is progressing and why things may have changed over time as they progressed through the intervention.

The CORTE interviewing framework developed to maximise the meaningful involvement of people with dementia will be used [65]. This guide consists of gaining **CO**nsent, maximizing **R**esponses, **T**elling the story, and **E**nding on a positive note. All facilitators/co-facilitators (*n* =9) as well as the older adults (*n* = 10) supporting the delivery of the exercise component will also be interviewed to capture their experiences of delivering and facilitating the intervention and identify any potential areas for improvement. In total, 54 interviews will be undertaken. Table 1 presents a summary overview of participants who will be interviewed, and the time point for these interviews.

**Table 1 Tab1:** Overview of the qualitative data collection process

Participants	Number interviewed Week 4-5	Number interviewed weeks 11-12	Number interviewed post-intervention Weeks 16–19	Total number of interviews
**People with dementia**	5 (CST)	5 (Physical Exercise)	10	20
**Caregivers**	5	0	10	15
**Facilitators and co-facilitators**			4 (CST) 2 (Physical Exercise) 2 (Community Dementia Awareness programme) 1 (GP Prepared programme)	9
**Older adults**			10	10
**Totals**	10	5	39	54

### Main trial outcome measurements

Although this is a feasibility study, we will explore the feasibility and acceptability of a range of secondary outcome measurement tools for use in a future definitive trial. A summary of these measures and the participant from which the outcome will be collected and recorded is presented in Table 2, while Table 3 presents a summary overview of how the pilot may inform a future definitive trial.

**Table 2 Tab2:** Summary overview of secondary outcome measures for future definitive trial

**People with dementia: Data collected at baseline and post 15-week intervention**	
**Quality of Life-Alzheimer’s Disease (QoL-AD)** [66]. The QoL-AD is a brief, 13-item measure designed specifically to obtain a rating of the person’s quality of life from either the person living with dementia and/or the caregiver [66]. For people with dementia, the questionnaire is completed during an interview that usually takes 10–15 min. The QoL-AD has very good psychometric properties and can be completed with people with a wide range of severity of dementia [67]. Internal consistency is good with a Cronbach’s alpha coefficient of 0.82 [67]. The scale has good content validity, and it also correlates well with the Dementia Quality of Life scale (0.69) and with the Euroqol-5D scale (0.54), indicating good criterion concurrent validity [67].	
**Mini-Mental State Examination (MMSE)** [68]. The MMSE consists of questions covering 11 domains. It is a simplified, scored form of the cognitive mental status examination, which assesses the cognitive aspects of mental functions.	
**The Geriatric Depression Scale–Short Form (GDS-15) **[69]. This is a 15-item self-completed questionnaire or administered interview used to measure depression in older adults and takes 5–7 min to complete. Mitchell et al. [70] completed a meta-analysis on the diagnostic accuracy, clinical utility and added value of the GDS in primary care. They concluded that the GDS-15 has acceptable sensitivity and specificity (81.3 and 78.4%, respectively), “good” clinical utility for screening and should be used in the diagnosis of late-life depression in primary care.	
**Stigma Impact Scale (SIS)** [71]. The SIS has 24 items and is completed by people with dementia to measure the perceived stigma inherent in progressive neurological diseases. The SIS can be administered via interview or self-completed and on average takes 10 min to complete. The internal consistency has a Cronbach’s alpha of 0.89, indicating good reliability [71]. Construct validity scores range from 0.44 to 0.84 [71].	
**Positive Psychology Outcome Measure (PPOM)** [72]. The PPOM is used to measure hope and resilience in people with dementia. It consists of 16 items designed for either self-completion by participants or completion via an interview and takes 5–10 min to complete. The internal consistency has a Cronbach’s alpha of 0.94, indicating excellent reliability [72]. The PPOM remained moderately stable over a 1 week period (ICC: 880), and factor analyses indicated a two-factor structure solution with acceptable fit indices [72]. The PPOM was developed from the Resilience Scale of Wagnild and Young [73], an instrument which scored highly in Windle et al. [74] review as a good measure of resilience.	
**EQ-5D-5L** [75]. The EQ-5D-5L is a 6-item standardized questionnaire that measures self-reported generic health status. The scoring system translates the quality of life scores into an economic value. Domain responses and utility scores have good test-retest reliability (ICC, 0.777; agreement, 76.4–98.1%) [76]. Scores of domains of the EQ-5D-5L correlated significantly (*r*, 0.57–0.74) with the scores of the SRS-22r domains, supporting construct validity [76].	
**Fitbit** The Fitbit will allow participants’ sleep patterns and exercise activity to be monitored. Each Fitbit will be synced to a mobile device or PC. The Fitabase data management platform will be used to extract and aggregate participant data to facilitate analysis.	
**Caregivers: Data collected at baseline and post 15-week intervention**	
**Zarit Burden Interview (ZBI)** [77]. The ZBI is a 22-item self-completed questionnaire or administered interview used to assess the level of burden experienced by the primary caregivers of older people with dementia and people with disabilities. The ZBI takes on average 10 minutes to complete. It is a valid and reliable instrument with a Cronbach’s alpha value of 0.93; intra-class correlation coefficient for the test-retest reliability of 0.89 (*n* = 149) [78].	
**Short Sense of Competence Questionnaire (SSCQ**) [79]. The SSCQ is a 7-item self-completed questionnaire or administered interview, which measures the sense of competence the caregiver of a person with dementia has. The SSCQ takes on average 5 min to complete. It is a valid and reliable instrument with a Cronbach’s alpha value of 0.76 [79].	
**Dementia Knowledge 20 (DK-20)** [80]. The DK-20 is a 20-item self-administered questionnaire, which measures the knowledge people have regarding dementia. It is a 20-item self-administered questionnaire that takes on average 15 min to complete. Convergent validity reveals significant correlation between the DK-20 scale and the ADQ calculated using Spearman’s one-tailed test, *r*(175) = 0.36, *p* < 0.001 [80]. Test-retest reliability for the total scale is ICC = 0.73, *p* < 0.001, which indicated substantial reliability of the scale [80].	
**Resource Utilization in Dementia-Lite (RUD-Lite)** [81]. The RUD-lite questionnaire consists of 25 items, and measures healthcare resource utilization among older adults with dementia and their caregivers, and time spent on formal and informal care by caregivers. The questionnaire is completed by the primary caregiver of the person with dementia and takes on average 15 minutes to complete. Wimo et al. [82] found the estimations provided by primary caregivers completing the RUD-lite to be accurate. The agreement between diaries and recall estimates was high for personal ADL (intra-class correlation (ICC) 0.93), supervision (ICC 0.87) and total time (ICC 0.91) and lower but acceptable for instrumental ADL (ICC 0.75) [82].	
**Adult carer quality of life (AC-QoL)** [83]. The AC-QoL is a 40-item questionnaire, which measures the overall quality of life of adult caregivers over 8 domains: support for caring, caring choice, caring stress, money matters, personal growth, sense of value, ability to care, and caregiver satisfaction. The questionnaire takes 10 minutes to complete. Construct validity using exploratory factor analysis was conducted by Negri et al. [84] using the Kaiser–Meyer–Olkin (KMO) measure with a total score of 0.90, and all KMO values for single items were higher than 0.70, thus above the acceptability limit of 0.50 [84]. Cronbach alpha scores for the eight subscales range from 0.79 to 0.90, showing acceptable to excellent levels of reliability; alpha coefficient for the AC-QoL summed score was also excellent (0.93) [84].	
**Older people: Data collected at baseline and post 15-week intervention**	
**Dementia Attitudes Scale (DAS)** [85]. The dementia attitude’s scale is a 20-item questionnaire that measures attitudes towards dementia of members of the public, working professionals, and students. The DAS measures attitudes towards dementia of members of the public, working professionals, and students. DAS correlates significantly with scales that measure ageism and attitudes toward disabilities and has a Cronbach’s alphas ranging from 0.83 to 0.85 [85].	
**Dementia Knowledge-20 (DK-20) **[80].

**Table 3 Tab3:** Summary overview of how the pilot may inform a future definitive trial

Pilot study-feasibility and acceptability of:	Informing a future RCT
Intervention content & delivery	Intervention content and modes of delivery finalised
Participant recruitment	An optimal participant recruitment strategy identified
Training requirements	Research, facilitator and older adult training requirements determined
Standard operating procedures (SOPs)	SOPs developed for all study processes
Data collection tools (quantitative & qualitative)	Quantitative secondary outcome measurement tools, economic data collection tools and qualitative interview guides confirmed
Fidelity assessment procedures	Fidelity assessment procedures finalised
FITBIT	Feasibility and acceptability of using Fitbit with people with dementia confirmed
RCT protocol	RCT protocol developed

### Adverse events

In this study, the definition of an adverse event will be similar to that used in the PRINCE study, i.e. ‘Any acute alteration in the patient’s physiological condition’ [86]. It is not anticipated that participants will be at risk of experiencing an adverse event, and participants with dementia will be required to confirm that their GP has been informed and given them permission to participate in the study. Furthermore, the physical exercise programme will be individualised and tailored to each individual participant based on an exercise assessment undertaken by the physical exercise specialist and his/her ongoing weekly monitoring of participants. However, in the unlikely event that an adverse event occurs, this will be recorded by facilitators or members of the research team on an Adverse Event Reporting Form and reported to the participant’s GP, as all clinical responsibility rests with those providing routine clinical care.

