**Fig. 2 Fig2:**
[figure not shown]
Overview of the CREST intervention components

In this feasibility study, the ‘Making a difference’ CST programme developed by Spector et al. [12] will be used. This programme consists of 14 sessions delivered over the first 7 weeks of the intervention. In CREST, participants with dementia will attend two 1 h sessions per week and each session will include approximately five participants. Sessions will include a focus on the use of reminiscence and providing triggers to aid recall, stimulating language and executive functioning and being person-centred.

A health care professional trained to deliver the programme using the CST manual and supported by a co-facilitator will facilitate each session. The role of the co-facilitator will be to help set up the class and support, prompt and encourage participants to adhere to the programme.
2)*Physical exercise programme*

An exercise programme, based on the PRINCE structured exercise programme [60] modified to meet the needs of people with dementia, will be used. This exercise programme, delivered over 8 weeks (after the CST programme), is a total of 12 h in duration: 1 h session a week for 4 weeks and 2 h sessions a week for 4 weeks (see Fig. 2). The programme is designed to be delivered in a group class and consists of a combination of aerobic and strength training exercises appropriate for people with dementia and education content specific to exercising. A physical exercise specialist supported by an exercise manual will facilitate the programme. Older adults from the community will support participants with dementia to undertake the exercises. The older adults will be invited to assist in the exercise sessions if they are:
> 60 years of ageLiving in the communityDo not have a diagnosis of dementiaWilling and capable of undertaking the exercise programmeWilling to support people with dementia to undertake the exercise programmeAble to speak in and read EnglishAble to give informed consent

These older adults, who form part of the intervention, will assist people with dementia by prompting them through their exercises and providing support, encouragement as well as social interaction and engagement. They will also assist people with dementia to record and track their exercise progress.

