The exercise specialist will assess the progress, duration and intensity of the programme for people with dementia throughout the intervention, in order to increase participants’ exercise capacity gradually. In week 1, participants with dementia will be asked to identify specific exercise-related goals they wish to achieve by the end of the programme. These will be reviewed in weeks 4 and 8. The exercise programme will begin with 10 × 3-min circuits. Participants with dementia will start at a station and rotate to the next station until all 10 circuits are completed. Each person with dementia will undertake the exercise at each station 8–10 times with three repetitions. At the end of 3 min, the person will record their exercises and move to the next station. In week 3, the exercise specialist will assess participants and prescribe weights for strengthening. Participants will be encouraged to complete some of the exercises at home and record these in a home exercise diary. In addition, each person with dementia will be asked to wear a Fitbit wearable activity tracker to measure changes in exercise activity and sleep quality before, during and after the physical exercise programme. Researchers will assist participants to set up their Fitbit and how to access their exercise performance on the tracker. The feasibility and acceptability of wearing this device as well as the extent to which the Fitbit acted as an exercise motivational tool will be captured via qualitative interviews.
3)*Dementia education programme*

This programme consists of three elements:
Community dementia awareness programme

This programme is targeted at members of the public in the wider community. It is designed to provide information on dementia, create positive action for dementia and tackle negative attitudes toward dementia. This programme, based on the Irish Health Service Executive’s [61] *Dementia: Understand Together* campaign will be 1 h in duration. It will be delivered and co-facilitated by dementia champions trained to deliver the programme. The programme will include information about dementia prevalence and impact, signs and symptoms, risk factors, and stigma and explores how communities can support the health and well-being of a person with dementia and their family.
(b)Caregiver programme

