### Sample size

As this is a non-randomised feasibility study, a formal sample size calculation is not required [88]. The aim is to recruit a purposive sample of 10 people with mild to moderate dementia and their primary caregivers (*n* = 10) (20 participants in total), who meet the inclusion criteria, to participate in the CREST intervention. The flow of participants through the study is presented in Fig. 3.

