### Recruitment

The initial recruitment plan involved creating a list of GP practices from the HRB Primary Care CTNI within (i) a 30-km radius of the city centre, (ii) having a population of not less than 2500 and (iii) having at least one whole time equivalent practice nurse. These practices were then contacted and invited to respond to an expression of interest regarding participating in the pilot study and to be contacted by a member of the research team. The latter inclusion criteria (ii and iii) were based on the optimal recruitment strategies used in the PRINCE study [60].

GP practices expressing an interest in taking part were asked to contact potential participants with dementia and their primary caregiver (i) informing them of the study, (ii) seeking their consent to participate and (iii) including consent to be contacted by a member of the research team. Participants willing to participate were then to be invited to meet the research team, where consent would be reconfirmed, and participants screened to confirm eligibility and baseline and feasibility data collected using the tools outlined in Table 2. Over a 10-week period, this recruitment strategy yielded only two GP practices out of 14 eligible practices. After another 8-week period, these practices were able to identify 17 participants with dementia who were eligible to participate and consented to be contacted by the research team. Of these, five participants with dementia and their caregivers consented to participate. However, two people with dementia and their caregivers subsequently withdrew, and the remaining six participants (three people with dementia and their caregivers) were retained within the study but an alternative recruitment strategy was then devised as outlined below.

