The revised recruitment strategy involves contacting the gatekeepers of local dementia advocacy and health care organisations to identify any potential people with dementia and their caregivers who might be interested in participating in the CREST study. This will include The Alzheimer Society of Ireland, Western Alzheimer’s and HSE carer’s organisations. The same steps used when recruiting the GP’s will be implemented (i) informing potential participants about the study, (ii) seeking their consent to participate and (iii) including consent to be contacted by a member of the research team. Participants willing to participate will then be invited to meet the research team, where consent will be reconfirmed, including permission to contact the participants GP to confirm their eligibility to participate. Baseline and feasibility data will then be collected using the tools outlined in Table 2.

Older adults (*n* = 10) in the community will be recruited to support the physical exercise element of the intervention using a variety of recruitment methods. These will include, for example, information posters in GP practices, pharmacies, active ageing/retirement groups, older people organisations and support charities, for example, Enable Ireland and St. Vincent de Paul.

Informed consent will be obtained from all participants in the study and process consent, which enables participants to have a collaborative role in the decisions regarding their ongoing participation [89], will be utilised throughout. Older adults, people with dementia and caregivers will all receive €20 toward travel expenses to facilitate meeting the researchers during recruitment, at each data collection point in the study, as well as when attending each respective session of the intervention.

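### The adverse-event definition, an acute physiological change in the patient, leaves out distress and does not clearly cover caregivers or the older-adult helpers, so harms may be under-recorded

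*Protocol article*

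**What the plan says.** The Adverse events section takes its definition from the PRINCE study, which the Abbreviations identify as a pulmonary rehabilitation programme. An event is "Any acute alteration in the patient’s physiological condition". The section expects no such risk and adds, by way of reassurance, that "participants with dementia will be required to confirm that their GP has been informed and given them permission to participate in the study". If an event does occur, facilitators or researchers enter it on an Adverse Event Reporting Form and inform the GP. Under Trial management, the steering group reviews adverse reports.

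Three groups are exposed to the programme. Sample size gives 10 people with dementia and 10 caregivers, and Recruitment adds 10 older adults from the community. The Intervention section says of the last group: "These older adults, who form part of the intervention, will assist people with dementia by prompting them through their exercises". They must be over 60 and capable of the exercise programme themselves. Exercise also takes place outside the sessions: "Participants will be encouraged to complete some of the exercises at home and record these in a home exercise diary".

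On the GP, the revised route under Recruitment provides that "consent will be reconfirmed, including permission to contact the participants GP to confirm their eligibility to participate".

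**The concern.** The definition suits the component it came with. The CREST exercise programme is itself adapted from PRINCE, and in a pulmonary rehabilitation study an acute bodily change in a patient is the natural thing to count. CREST is wider. It adds cognitive stimulation with reminiscence, a dementia education course for caregivers, a stigma scale and a depression scale for people with dementia, and volunteers over 60 who help in the exercise sessions. A person upset by a reminiscence session, a caregiver distressed by the course content, or a helper who falls would either lie outside the wording or depend on how a facilitator chose to read it.

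What is at stake is the harms record that the study hands to the definitive trial. A feasibility study is the place to test how harms will be recorded. A report of no adverse events under this definition would say nothing about distress and could be silent about up to two of the three groups.

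**Working it through.** The plan gives no event rate, and under Sample size it states that "a formal sample size calculation is not required". There is therefore no planned figure to reproduce. The check compares the text and adds a head count.

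**1. Kind of event.** The wording requires a change that is acute and physiological. Psychological distress is not physiological on any ordinary reading, so it is outside the definition for every group. Falls with injury and other acute bodily events are inside it, at least for people with dementia.

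**2. Persons covered.** People exposed: 10 with dementia + 10 caregivers + 10 helpers = 30. Facilitators and those attending the community and GP education events are left out of this count. The definition says *patient*, but later sentences of the section say *participant*, and the article uses that word in two ways:

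| Reading | Basis | Covered |
|---|---|---|
| *Patient* means the person with dementia | Wording of the definition | 10/30 = 33% |
| *Participant* as counted in Sample size (20 in total) | People with dementia and caregivers | 20/30 = 67% |
| *Participant* as used in Table 1, which lists older adults | All three groups | 30/30 = 100% |

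Within the exercise component, 10 people with dementia and 10 helpers take part, so the literal reading covers 10/20 = 50%. The article does not say which reading applies.

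**3. Place.** The definition sets no limit of place or time. An acute physiological event during home exercise meets it.

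**4. GP agreement.** Adverse events has the person with dementia confirm that the GP knows of the study and permits participation. Recruitment, revised route, has the team seek leave to contact the GP to confirm eligibility. The inclusion criteria make capability for the exercise component part of eligibility, so that contact bears on suitability for exercise. Under the initial route, "GP practices expressing an interest in taking part were asked to contact potential participants with dementia and their primary caregiver", so the practice was already involved. Both steps can be carried out and neither excludes the other. What is missing is a link between them.

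**The case against.** The best defence is that the article condenses a fuller protocol. The definition is described only as similar to the PRINCE wording, the operative sentences speak of participants, and the reporting form may be broader. Distress is not ignored either: the Ethics section promises a protocol to avoid upset, consent is revisited throughout, depression, stigma and caregiver burden are scored at both time points, and interviews are held during and after the intervention. The steering group sees adverse reports, and reasons for attrition are collected.

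Part of this stands. Form layout and prompts at each session may properly be left to the full protocol, and their absence is no fault. But the article does state its definition, so the definition can be judged as written. Scale scores, interviews and an ethical protocol are not event reporting: none of them yields a count of people harmed.

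A reader might infer more than the documents support:

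- *The GP is bypassed, or permission rests only on the word of a cognitively impaired person.* Step 4 of the check shows otherwise.
- *The definition misses home exercise.* It sets no limit of place, and the exercise specialist's weekly monitoring may bring home events to light.
- *Safety is under-recorded.* The text shows a risk, not its occurrence or size.
- *Progression is decided without regard to harms.* Table 4 has no safety item, but the steering group reviews adverse reports. A formal safety criterion in a single-arm study of 10 dyads is a matter of preference.
- *A confidence limit for zero events in 10 people measures the problem.* It would describe the small sample, not incomplete capture.

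**Conclusion.** The point holds for the definition. As worded, it excludes psychological distress for everyone and leaves the coverage of caregivers and helpers unclear: between 10 and 30 of the 30 people exposed are covered, depending on the reading. The 10 of 30 figure assumes that *patient* means only the person with dementia. The consequence is that harms may be under-recorded, by an amount the documents do not allow one to estimate. The conclusion also assumes that the form follows the published definition; if the form is already wider, the article's wording should be brought into line with it. The GP passages do not contradict each other and need only a cross-reference.

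**What to change.** Reword the definition and the Adverse Event Reporting Form in three respects:

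- name people with dementia, caregivers and older-adult helpers as covered;
- include psychological distress as well as physical events such as falls and injury;
- state that events count whether they arise in sessions or during home exercise.

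Report counts by group to the steering group, alongside the Table 4 criteria, when progression is considered. As a minor edit, cross-refer the Adverse events and Recruitment sections so that GP agreement is documented through the contact already planned.

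The cost is a few lines of text, a revised form and slightly more recording. More events will be reported, and the report should say that this follows from the broader definition. Sample size, design and intervention do not change.
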